## Abstract

**Background:**

The rising prevalence of childhood obesity poses a significant public health challenge in China, with rates among primary school students increasing from 6.8% in 2002 to 19% in 2020. Concurrently, coarse-cereal intake—a source of dietary fiber and bioactive compounds with potential protective effects against obesity—has declined markedly. School-based interventions represent a feasible strategy to address this issue. This protocol describes a cluster-randomized pragmatic controlled trial (pRCT) aimed at evaluating the effectiveness of a comprehensive intervention to increase coarse-cereal intake for obesity prevention among Chinese primary school students.

**Methods:**

A two-arm pragmatic cluster-RCT will be conducted in public primary schools in Huairou District, Beijing. Two schools will be randomly assigned to intervention or control groups, with 400 students (grades 3–4, aged 8–12 years) enrolled. The intervention group will receive a daily 50 g coarse-cereal substitution in school meals, aligned with Chinese dietary guidelines, alongside a multi-level nutrition education program targeting students, parents, and school staff. The control group will continue standard practices. Primary outcomes include changes in body mass index standard deviation score (BMI-SDS), body composition, waist circumference, and blood pressure, assessed at baseline, 3 months, and 6 months. Secondary outcomes encompass metabolic indicators and gut microbiota profiles in overweight/obese subgroups. Data will be analyzed using mixed-effects linear models, accounting for cluster effects. Implementation fidelity will be monitored through quantitative and qualitative methods.

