#### Sample size calculation

2.3.1

The primary outcome for sample size estimation was the Body Mass Index Standard Deviation Score (BMI-SDS). Due to the lack of previous studies on coarse-cereal interventions in this population, sample size was estimated based on prior research evaluating comprehensive interventions on obesity in primary school students. The calculations assumed 80% power (*β* = 0.20), a two-sided significance level of 0.05 (*α* = 0.05), standard deviation *σ* = 1.39, and effect size *Δ* 0.17. The resulting sample size was 180 students per school. Allowing for 10–20% attrition, the target enrollment per school was set at 190–200 students (18). The calculation formula used will be:

$$n=\frac{{\left(Z_{\alpha /2}+Z_{\beta }\right)}^{2}{\left(2\sigma^{2}\right)}^{2}[1+(m-1)\rho ]}{{\left(\mu_{1}-\mu_{2}\right)}^{2}}$$

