### Data collection

2.5

Data will be collected at three time points: baseline (T0), post-intervention at 3 months (T1), and at 6-month follow-up (T2, 9 months). The specific time points for each category of data collection are detailed in Figure 2.

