##### Primary outcome indicators

2.5.2.1

(1) Body Mass Index (BMI)

Height and weight will be measured using a calibrate stadiometer and digital scale, with students in light clothing and barefoot after fasting. BMI will be calculated as weight (kg)/ height^2^ (m^2^) and categorized according to Chinese reference standards.

(2) Body Composition

Measured using an 8-electrode, 4-frequency bioelectrical impedance analyzer (InBody 770, Biospace Co., Ltd.) validated for children to assess body fat and lean mass.

(3) Waist Circumference (WC)

Measured at the midpoint between the lowest rib and iliac crest with a non-elastic tape, in triplicate, to 0.1 cm accuracy.

(4) Blood Pressure (BP)

Measured using an electronic sphygmomanometer (HBP-1300, Omron) after 5 min of rest; two readings will be taken with a 3-min interval. Childhood obesity is a significant risk factor for elevated blood pressure, which serves as a sentinel indicator for assessing cardiometabolic risk. By incorporating blood pressure measurements, this study aims to investigate whether increasing dietary fiber intake through coarse-cereal consumption offers potential benefits in improving early cardiovascular risk markers associated with obesity.

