#### Subgroup and sensitivity analyses

2.6.3

Pre-specified subgroups included se and baseline BMI category. Three way interactions (group x time x subgroup) tested effect modification, with Bonferroni correction (*α* = 0.025). Per-protocol analysis excluded participants with <50% intervention adherence. Complete-case analysis will be conducted to assess robustness to missing data.

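### Four outcome domains are all called primary with no rule for combining them, and the article conflicts on whether the BMI primary is BMI-SDS or BMI in kg/m²

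*Protocol article*

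**What the plan says.** **Which outcomes are primary.** The Abstract (Methods) states: "Primary outcomes include changes in body mass index standard deviation score (BMI-SDS), body composition, waist circumference, and blood pressure". Section 2.5.2.1 lists four items under its primary-outcome heading:

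- BMI, computed in kg/m² "and categorized according to Chinese reference standards"; the standard deviation score is not mentioned there.
- Body composition, from an impedance device "validated for children to assess body fat and lean mass".
- Waist circumference: "Measured at the midpoint between the lowest rib and iliac crest with a non-elastic tape".
- Blood pressure, for which "two readings will be taken with a 3-min interval"; systolic and diastolic pressure are not named as separate outcomes.

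**Which outcome sized the trial.** Section 2.3.1: "The primary outcome for sample size estimation was the Body Mass Index Standard Deviation Score (BMI-SDS"). The two-sided 0.05, the SD of 1.39 and the difference of 0.17 are all given there for that outcome.

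**How outcomes are tested.** Section 2.6.2 fits a linear mixed model with group, time (T1, T2) and their interaction, and with the baseline value as a covariate. It names the interaction as the primary test. Section 2.5 gives the visits as "baseline (T0), post-intervention at 3 months (T1), and at 6-month follow-up (T2, 9 months").

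**Error control.** Section 2.6.3 says the three-way subgroup interactions "tested effect modification, with Bonferroni correction" at 0.025. No other adjustment, ordering or success rule is stated.

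**The concern.** With several primary outcomes and no decision rule, a favourable result on any one of them can be reported as success on a primary outcome. The nominal 5% then no longer describes the risk of a false claim. The Discussion says positive findings are meant to inform national school-meal policy, so what counts as effective needs to be fixed in advance. The plan does fix a correction, but only for the two subgroup factors, which leaves the subgroup tests better protected than the main claim.

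The BMI conflict adds to this. A reader of section 2.5.2.1 would take BMI in kg/m² as the primary. A reader of the Abstract or section 2.3.1 would take BMI-SDS. The assumed difference and SD apply only to BMI-SDS, so the sizing does not carry over to another BMI measure.

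**Working it through.** **1. Inputs.**

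- Domains labelled primary: 4 (Abstract; section 2.5.2.1).
- Measures: BMI 1, body fat 1, lean mass 1, waist 1, blood pressure 1, so 5. Counting systolic and diastolic pressure separately gives 6; that split is an assumption.
- Tests per outcome: 1, the interaction (section 2.6.2).
- Alpha per test: 0.05. It is stated only in section 2.3.1, for BMI-SDS; its use for the other outcomes is an assumption.
- Correlation between test statistics: not given, so a range is shown.

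**2. The plan's own correction.** Two subgroup factors (sex and baseline BMI category) give 0.05 / 2 = 0.025, which matches section 2.6.3. The same logic applied to the primary outcomes would give 0.05 / 4 = 0.0125 for four tests or 0.05 / 5 = 0.01 for five. The document states neither.

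**3. Independent tests.** P(at least one false positive) = 1 − (1 − 0.05)^m.

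- m = 4: 1 − 0.95⁴ = 0.185
- m = 5: 1 − 0.95⁵ = 0.226
- m = 6: 1 − 0.95⁶ = 0.265

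**4. Correlated tests.** Simulation of m normal test statistics with common correlation r, each rejected when |z| > 1.96; 400,000 draws per case.

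| Assumed r | 4 tests | 6 tests |
|---|---|---|
| 0.3 | 17.3% | 24.2% |
| 0.5 | 15.7% | 20.7% |
| 0.7 | 13.1% | 16.4% |
| 0.9 | 9.3% | 10.9% |

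Five tests lie between the two columns. Every case exceeds 5%.

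**5. Which BMI measure.**

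| Place | Measure |
|---|---|
| Abstract, Methods | BMI-SDS, listed as primary |
| Section 2.3.1 | BMI-SDS, used for sizing |
| Section 2.5.2.1, item 1 | BMI in kg/m², also categorised; no SDS |

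Two places agree and the section that defines the primary outcomes differs. The Chinese reference it mentions is tied to the categories; no passage says which reference the SDS uses.

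**6. What the named primary test measures.** With T0 as a covariate and time at two levels, let d1 and d2 be the adjusted group differences at T1 and T2. The interaction is d2 − d1, on one degree of freedom. If the intervention lowers BMI-SDS equally at both visits, d1 = d2 and the interaction is zero. It therefore tests whether the effect changes between visits, not whether there is an effect at either. Naming a primary visit would not be enough without changing this test.

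**7. Cost of keeping all outcomes primary.** For a test with a true 80% power at 0.05, Bonferroni for 4 tests lowers power per test to 62%, or needs 1.42 times the sample. For 6 tests the figures are 56% and 1.54 times.

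**The case against.** **Multiplicity is often left to the analysis plan, and this is a condensed article.** This has force: a correction may exist in a document not shown, and silence alone would be weak ground. But the article itself fixes four domains as primary and itself fixes a correction for subgroups only. The point rests on what it states.

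**BMI-SDS is effectively the sole primary because it sized the trial.** Section 2.3.1 calls it primary for sample size estimation only. The Abstract and section 2.5.2.1 still give the others equal standing.

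**The alpha of 0.05 is not assigned to every outcome.** This is correct, and the figures are conditional on it. No other level is offered for the main comparison.

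A reader might also infer four stronger things, none of which the document supports:

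- *That two visits double the tests to twelve.* Section 2.6.2 names one interaction test per outcome.
- *That raw BMI has replaced BMI-SDS throughout.* The Abstract lists BMI-SDS as primary; this is a conflict between sections.
- *That the BMI primary is categorical and unfit for a linear model.* Section 2.5.2.1 calculates BMI, which is continuous, and also categorises it. The categories have uses elsewhere, such as the subgroup by baseline BMI category.
- *That an age difference between the schools would pass straight into a raw-BMI comparison.* Section 2.6.2 adjusts for age and for the baseline value of the outcome.

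**Conclusion.** The point holds on two counts.

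First, four domains (at least five measures) are primary with no hierarchy, joint-success rule or alpha split. At 0.05 per outcome, the chance of at least one false-positive primary is 18.5% to 22.6% for four to five independent tests, and 26.5% if blood pressure counts twice. Under assumed common correlations it is about 16% to 21% at 0.5 and 9% to 11% at 0.9, for four to six tests. The exact figure depends on a correlation the document does not give; that it exceeds 5% does not, within the range examined. These figures also take each single test to hold its nominal 5%, which one school per arm does not guarantee.

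Second, the sections disagree on whether the BMI primary is BMI-SDS or BMI in kg/m². This is a mismatch to be reconciled and does not show that the sized outcome has been dropped.

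Both should be corrected. Any single-visit primary also requires a change to the primary test in section 2.6.2.

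**What to change.** 1. Name one primary outcome: BMI-SDS, analysed as continuous, with its reference standard stated, at one named visit. T1, the end of the intervention, is an example. If T2 is preferred, first reconcile its timing, since the Abstract gives the last visit as 6 months and section 2.5 labels it 9 months.
2. In section 2.6.2, make the primary test the adjusted between-group difference at that visit. Keep the group-by-time interaction as a secondary question about whether the effect persists.
3. Move body composition, waist circumference and blood pressure to secondary, either Holm-adjusted or labelled exploratory.
4. Write BMI-SDS in section 2.5.2.1, item 1, to agree with the Abstract and section 2.3.1, and keep BMI category as descriptive and for the subgroup.
5. Since the study began in March 2026, date the amendment and make it before outcome data are examined by arm.

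The cost is protocol wording. The real loss is that the other three domains can no longer be claimed as primary successes. If the sponsor wants to keep them all primary, an explicit hierarchy or alpha split is needed, with the loss of power per test shown above where Bonferroni is used.

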**Discussion:**

This trial will address a critical evidence gap by testing a culturally adapted, school-based intervention to promote coarse-cereal consumption. If effective, the findings will inform the integration of coarse cereals into national student meal policies, contributing to sustainable obesity prevention strategies in China. The study design emphasizes practical implementation through a socio-ecological framework, with potential for scalability.

**Clinical trial registration:**

Identifier ChiCTR2500114773.

## Introduction

1

The prevalence of overweight and obesity among children and adolescents has increased substantially worldwide. According to the World Obesity Federation, the combined prevalence of overweight and obesity among individuals aged 5–19 years rose from approximately 8% in 1990 to nearly 20% in 2022 (1). In 2022, more than 390 million children and adolescents in this age group will be classified as overweight, including approximately 160 million who will be obese. A similar trend has been observed in China, where the prevalence of the overweight and obesity among primary school students increased from 6.8% in 2002 to 19% in 2020 (2, 3). This increase has occurred not only in urban areas but also in rural regions (3). Childhood obesity is associated with an elevated risk of adverse health outcomes later in life, including type 2 diabetes, cardiovascular diseases, and metabolic syndrome, thereby increasing the long-term economic burden and placing substantial pressure on healthcare systems (4, 5).

Dietary factors play a critical role in the development of obesity, and cereals constitute a major component of the traditional Chinese diet (6). Cereals are commonly classified as refined cereals or coarse cereals. Refined cereals undergo extensive processing, resulting in substantial losses of vitamins, minerals, and dietary fiber, with starch remaining the predominant component. High consumption of refined cereals has been associated with an increased risk of overweight and obesity (7–10). In contrast, coarse cereals are minimally processed or unprocessed and share characteristics with whole grains, retaining higher levels of dietary fiber and various bioactive compounds (9). Historically, coarse cereals represented a major staple in the Chinese diet. However, their consumption has declined markedly over recent decades. In 1982, Chinese children aged 6–17 years consumed an average of 114.3 g of coarse cereals per day, whereas intake decreased to only 8.0 g per day by 2020 (3, 11).

Several studies have suggested that increasing the intake of fiber-rich cereal foods may be beneficial for the prevention and control of overweight and obesity among school-aged children (12–16). For example, a school-based whole-grain provision program combined with parental education in Malaysia was associated with reductions in BMI z-scores and body fat percentage over a six-month intervention period; compared with the control group, children in the intervention group experienced a 2.6% reduction in body fat percentage and a 2.4 cm decrease in waist circumference (17). Similarly, the Healthy School Meals Initiative in the United States has been shown to improve dietary quality and was associated with lower prevalence rates of overweight and obesity in participating schools (18).

Taken together, the increasing prevalence of childhood obesity in China, the marked decline in coarse-cereal consumption, and the potential of schools as effective intervention settings underscore the importance of the present study. By evaluating the effectiveness of a school-based coarse-cereal intake intervention, this study aims to address existing evidence gaps and generate evidence to inform strategies for childhood obesity prevention in China.

## Methods and analysis

2

This study protocol is reported in accordance with the Standard Protocol Items: Recommendations for Interventional Trials (SPIRIT) 2025 guidelines.

### Study design

2.1

This study is designed as a parallel-group, cluster-randomized pragmatic controlled trial (pRCT) with two arms: an intervention group receiving a coarse-cereal intake intervention and a control group continuing usual dietary practices (19). Recognizing the real-world constraints of school-based dietary interventions, we adopted a pragmatic design to evaluate the effectiveness of the intervention under routine conditions. Consequently, while blinding of participating students, parents, and school staff is inherently unfeasible due to the nature of the dietary intervention, this limitation is an accepted characteristic of the pRCT framework aimed at maximizing external validity. To mitigate potential assessment bias within this pragmatic framework, outcome assessors responsible for anthropometric and biological measurements will remain blinded to group allocation. The study protocol adheres to the CONSORT 2025 extension for pragmatic trials to ensure methodological rigor and transparency (20, 21). The study commenced in March 2026, and the basic process of the intervention is illustrated in Figure 1.

**Figure 1 fig1:**
[figure not shown]
Flowchart of intervention process.

### Randomization and allocation

2.2

Clusters, defined as individual schools, serve as the unit of randomization. The study population is drawn from public primary schools in Huairou District, Beijing, where the prevalence of overweight and obesity among school-aged children exceeds 30%, highlighting the need for effective interventions.

Eligible schools met the following criteria: (1) Availability of an on-site cafeteria capable of providing daily breakfast and lunch to ensure consistent implementation of coarse-cereal substitution; (2) No dietary intervention programs implemented in the past year; (3) Enrollment of at least 150 students in grades 3–4 (ages 8–12) to ensure sufficient sample size per cluster, and (4) Approval from school administrators to participate in the trial.

Two schools meeting these criteria will be randomly assigned to either the intervention or control group using a computer-generated random number table (SAS 9.4).

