### Study population

2.3

All students in grades 3–4 at the selected schools will be screened for individual eligibility according to the inclusion and exclusion criteria. A total of 400 students will be enrolled, with 200 allocated to the intervention group and 200 to the control group, allowing for potential attrition.

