#### Outcome analysis

2.6.2

Analysis will be performed following the intention-to-treat principle. Mixed-effects linear models (MLMs) will be used to evaluate changes in outcomes from baseline (T0) to post-intervention (T1) and follow-up (T2). The models will include group (intervention/control), time (T1, T2), and the group-by-time interaction as fixed effects, with the baseline value (T0) of the respective outcome included as a covariate. Individual-level intercepts will be fitted as random effects to account for repeated measurements, and school will be included as a random effect to adjust for the cluster-randomized design. The models will be further adjusted for prespecified covariates, including age, sex, and baseline physical activity level. The primary test for intervention effect will be the significance of the group-by-time interaction term.

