### Implementation evaluation

2.7

Implementation of fidelity and exposure will be assessed to validate intervention effects. Metrics will include:

(1) School-level compliance with the meal plan (e.g., provision of ≥50 g of coarse cereals per student per day).(2) Participant attrition rates at T1 and T2.(3) Comparison of overweight/obesity outcomes between compliant and non-compliant schools.(4) Individual-level adherence, which will be assessed based on the 3-day 24-h dietary recall data collected at T1. High adherence is defined as an estimated average daily coarse-cereal intake of ≥40 g, while low adherence is defined as an intake of <25 g.(5) A prespecified subgroup analysis comparing outcomes between participants with high adherence and those with low adherence.

Paired *t*-tests and standardized regression coefficients will be used to evaluate outcome changes and the impact of confounding factors. Analyses will adjust for confounding factors (e.g., age, sex, baseline BMI). The impact intensity of each variable will be determined using standardized regression coefficients.

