### Limitations

3.4

Several limitations should be considered within the context of this pragmatic design. First, the 3-month intervention period may not capture long-term effects, although the 6-month follow-up provides a partial evaluation of maintenance. Second, as a pilot pragmatic cluster-randomized trial (pRCT) conducted in only two primary schools in suburban Beijing, the findings are primarily applicable to similar settings with on-site cafeterias. While the limited number of clusters may increase the risk of baseline imbalance, this pilot scale was necessary to test the feasibility and implementation fidelity of the intervention before wider rollout. Third, consistent with the nature of pragmatic trials conducted in real-world settings, blinding of participants and school staff was not feasible. Although this introduces the potential for performance bias, it reflects the actual conditions under which such dietary interventions would be implemented. To mitigate detection bias, we strictly maintained blinding of outcome assessors for anthropometric and biological measurements. Finally, unmeasured confounders, such as family lifestyle factors not captured in current assessments, may influence outcomes, a challenge common to school-based community interventions.

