## Conclusion

4

This school-based pragmatic randomized controlled trial (pRCT) addresses a critical public health need by evaluating a contextually appropriate coarse-cereal intervention to prevent childhood obesity in China. By emphasizing cultural relevance, multi-level engagement, and real-world applicability, the study is expected to provide actionable evidence on both the effectiveness and feasibility of updating national student meal policies. While explanatory trials establish efficacy under ideal conditions, this pRCT is designed to inform how such interventions perform within the complex constraints of routine school environments. Despite inherent limitations, the protocol’s rigorous design—including cluster randomization, blinded outcome assessment, and comprehensive quality control—ensures that results will be robust and directly translatable to policy, ultimately contributing to the health of Chinese school-aged children.

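### With one school per arm, intervention and school cannot be separated, so the planned school random effect cannot adjust for clustering and the effectiveness and policy claims go beyond what two schools support

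*Protocol article*

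**What the plan says.** On design, section 2.2 of the protocol article reads "Clusters, defined as individual schools, serve as the unit of randomization", and then "Two schools meeting these criteria will be randomly assigned to either the intervention or control group". Section 2.3 gives the numbers: "A total of 400 students will be enrolled, with 200 allocated to the intervention group and 200 to the control group". Each arm is therefore one school of 200 students.

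On analysis, section 2.6.2 specifies a mixed model for T1 and T2 with group, time and their interaction, the T0 value as covariate, a student random intercept, and adjustment for age, sex and baseline physical activity. It adds that "school will be included as a random effect to adjust for the cluster-randomized design". The primary test is the group-by-time interaction.

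On interpretation, section 3.4 describes the study "as a pilot pragmatic cluster-randomized trial (pRCT) conducted in only two primary schools in suburban Beijing" and concedes: "While the limited number of clusters may increase the risk of baseline imbalance". It also limits applicability to similar settings, gives feasibility and fidelity as the reason for the small scale, and names unmeasured confounders. The Abstract, 2.1 and 3.1 state an effectiveness aim. The Conclusion says the rigorous design, cluster randomization included, "ensures that results will be robust and directly translatable to policy".

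On implementation, metric (3) in section 2.7 is: "Comparison of overweight/obesity outcomes between compliant and non-compliant schools".

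**The concern.** A cluster-randomized comparison draws its error term from variation between clusters in the same arm. With one cluster per arm there is no such variation to observe. A random effect for school then has nothing to estimate, yet 2.6.2 presents it as the adjustment for clustering. A reader of the results would take the p-value and confidence interval as allowing for school differences when they do not.

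At stake is whether a residual difference between two particular schools, in level or in change over the study, is reported as the effect of coarse cereals and nutrition education, with understated uncertainty, in support of national school-meal policy. Metric (3) in 2.7 meets the same obstacle: only one school receives the meal plan, so comparing compliant with non-compliant schools either cannot be done or repeats the comparison of arms.

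**Working it through.** **Inputs.** Two schools, one per arm (2.2, 3.4). 200 students per school enrolled (2.3); 180 per school before attrition (2.3.1). Two-sided α = 0.05 (2.3.1). ICC: the symbol appears in the 2.3.1 formula without a value, so 0.001 to 0.05 is assumed here.

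**The plan's own figure.** The 180 per school does not reproduce. The standard two-mean formula with SD 1.39 and Δ 0.17 gives 2 × (1.960 + 0.842)² × 1.39² / 0.17² ≈ 1,050 per arm before any design effect. That is a separate matter; 180 serves below only as the cluster size m.

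**Step 1: can school be separated from group?** The design matrix with intercept and group has rank 2. Adding school leaves the rank at 2. Between-school df = 2 clusters − 2 arms = 0. In three trial REML fits with one school per arm, the school variance stayed at the optimizer's starting value with a standard error of about 1.4 × 10⁷, so the data carried no information on it. There are only two possible allocations, so the smallest two-sided randomization p-value is 1.0. None of this depends on an ICC.

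**Step 2: group difference at one visit, if software sets the school variance to zero.** Design effect DE = 1 + (m − 1) × ICC with m = 180. Type I error = 2 × [1 − Φ(1.96/√DE)]. The true standard error is √DE times the reported one.

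| Assumed residual ICC | DE | √DE | Type I error |
|---|---|---|---|
| 0.001 | 1.179 | 1.09 | 7% |
| 0.005 | 1.895 | 1.38 | 15% |
| 0.01 | 2.79 | 1.67 | 24% |
| 0.02 | 4.58 | 2.14 | 36% |
| 0.05 | 9.95 | 3.15 | 53% |

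Simulation for the last four rows gave 15%, 25%, 38% and 55%.

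**Step 3: the primary test.** With outcomes at T1 and T2, the group-by-time term compares the T2 − T1 change between arms. A school random intercept enters both visits equally and cancels, so the Step 2 figures do not apply to it. A school-by-time effect does not cancel, and with one school per arm it coincides with group-by-time. In simulation with 180 students per school, if schools account for 0.5%, 1% or 2% of the variance of the within-student T2 − T1 change (again assumed), the type I error is 16%, 24% or 37%. With no school share it was 4.5%, close to nominal.

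**The case against.** The protocol is more candid than a quick reading suggests. A reader might infer that the limitations admit only baseline imbalance. In fact 3.4 also says there are only two schools, restricts applicability, gives a feasibility rationale and concedes unmeasured confounders. A reader might also infer that the Abstract promises evidence ready for policy. Its discussion is conditional on the intervention proving effective, as is 3.3, which goes on to suggest phased rollout; the unconditional wording is in the Conclusion.

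Nor is it right that every difference between the schools would pass as an intervention effect. Eligibility requires an on-site cafeteria and no dietary programme in the past year, and the model adjusts for the child's baseline outcome, age, sex and baseline activity. Only what remains after that is inseparable.

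The error rates need the same care. They hold only if the school variance is set to zero, which is one software outcome and not the one seen in the trial fits. They depend on a residual ICC that the document does not give, and at 0.001 the inflation is small. The table is not for the primary test.

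All of this stands and limits the claim. It does not answer the core: covariates and eligibility criteria cannot supply between-school degrees of freedom, and 3.4 nowhere says that the school effect cannot be separated from the intervention. Imbalance is a chance event; this confounding is certain by design. The plural references to schools in 2.4.4 and 2.7 do not show that further schools exist.

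**Conclusion.** The point holds and needs correction. Intervention and school are completely aliased, so the statement in 2.6.2 about the school random effect is wrong as written. No separate analysis plan could make the variance estimable from two schools. The same is true of school-by-time variation for the primary test. This conclusion is structural and needs no ICC.

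The size is illustrative: about 7% to 53% type I error for a single-visit group difference over assumed residual ICCs of 0.001 to 0.05, and 16% to 37% for the interaction if schools carry 0.5% to 2% of the variance in change. Both ranges assume that school variation is left out of the standard error.

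The pilot and feasibility framing in 3.4 does not fit the effectiveness aim in the Abstract, 2.1 and 3.1, and contradicts the assurance in the Conclusion. The 2.7 metric is a secondary consequence of the same design.

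**What to change.** 1. In 2.6.2, delete the claim that the school random effect adjusts for clustering. State that between-school and school-by-time variance are not estimable. Report student-level estimates and intervals together with intervals widened under a stated range of assumed ICCs (for the group difference at one visit, multiply the standard error by √DE as in the table), presented as not confirmatory.
2. Carry the pilot label of 3.4 into the Abstract, 2.1 and the Conclusion. Add to 3.4 that the school effect cannot be separated from the intervention. Limit conclusions to feasibility, fidelity and preliminary estimates, and delete the policy assurance from the Conclusion.
3. In 2.7, delete metric (3), or replace it with day-level or class-level fidelity within the intervention school.

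The study began in March 2026 according to 2.1, and none of these changes needs additional schools. The cost is revised wording, one sensitivity table and a weaker claim. The changes do not remove the confounding; they bring the stated analysis and conclusions into line with what two schools can support.
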